#### Rapid HIV testing and assurance of linkage-to-care

When approaching ED patients about the study, the RAs will inform them that for the study they will have an HIV test after completing the post-information questionnaires. They also will be informed that their test result must be negative to be enrolled in the longitudinal, follow-up portion of the study. The negative HIV test is required because one of the aims of this study is to assess retention of the information provided via pictorial brochure or video, which is pertinent only for those with a negative HIV test. Those who are HIV infected would not require repeat testing or receipt of this information.

After each patient has completed the initial questionnaires and received HIV/AIDS and HIV testing information from the pictorial brochure or video, the RAs will briefly describe the test procedures. The RAs will record the reasons for accepting or declining HIV testing (*See* Additional file 1). Those who decline testing will be provided with a brochure about HIV/AIDS and HIV testing that contains a list of places where they can be tested in their area. Those who agree to testing will sign a consent form which specifies that: (1) the participant will undergo HIV testing and the results of their test will be included in the study database; (2) participation in the longitudinal, follow-up portion of the study is contingent upon a negative HIV test; (3) the RA will obtain contact information for the participant to ensure attendance at the follow-up appointment and receipt of the final confirmatory test results (for those with a preliminary positive test); (4) the RA will initiate confirmatory testing for HIV for those who test preliminary positive for HIV; and (5) the RA will assist them in adhering to their follow-up visit. The consent form will also outline the follow-up procedures and participant responsibilities for the study.

The type of HIV testing conducted will vary by study site based on standard practice at each location. The Los Angeles and Providence sites will use fingerstick rapid HIV testing performed by the RA. The Birmingham and Cincinnati sites will use laboratory-based HIV testing. Participants will receive their test results during their ED study encounter. The RAs, as trained HIV test counselors, will provide post-test counseling and support for those with a preliminary positive HIV test result. The RA will coordinate with ED staff to obtain a phlebotomized sample for CD4+ count, Western blot, and viral load testing. We will adapt the testing, quality assurance, preliminary positive test, and assurance of linkage-to-care protocols from our prior studies, that include obtaining extensive contact information from the participant, providing multiple means of contacting study staff, written information detailing the appointments for follow-up, reminder telephone calls, and assistance with transportation to the follow-up appointment. The project manager, PI, and site investigators also will help to ensure linkage-to-care.

#### Follow-up assessments (months 10–54)

Potential participants meeting all study eligibility criteria (including a negative HIV test) will be invited to enroll in the longitudinal, randomized, controlled trial. Participants will complete the follow-up assessments via the automated telephone questionnaire system at 3, 6, 9 and 12 months post-enrollment. Prior to the due dates of each participant’s 3, 6, 9, and 12-month follow-up, the RAs will remind each participant by telephone, email, and letter that their follow-up is due, how to complete the follow-up, and who to contact for help. During the telephone assessments, participants will complete the HIV/AIDS and HIV testing knowledge, HIV risk-taking, and HIV testing utilization questionnaires. Participants who have difficulty with the telephone system can contact study staff and complete the assessments with their assistance. After completing each follow-up assessment, each participant’s gift card will be re-charged (in successively increasing amounts). Those who report to us that they no longer have their gift card will be sent a new one. Any participants who fail to complete the 3-month post-enrollment follow-up will be discontinued from the study. The recruitment quota will be adjusted to replace them as applicable at their respective study site.

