#### Information delivery and post-information delivery questionnaires

We will randomly assign patients in a 1:1 ratio into information delivery mode Arm 1 or Arm 2. As noted previously, the two arms will be stratified within language (English or Spanish) and health literacy level [22] (lower vs. higher) (*n* = 150/stratum). We will use block randomization techniques to ensure that there are equal numbers in each arm per study site and stratum using a centralized, random assignment computerized system. Randomization sequences by language and health literacy level will be posted on a secure website that RAs across all four sites will consult when assigning participants to study arms. The advantage of this approach is that we can monitor enrollment and balance within study arms and across study sites easily, address concerns as they arise, and permit efficient use of study resources. The two groups will differ by the following:Arm (1): HIV/AIDS and HIV testing video: Participants in Arm 1 will watch the video, “What do you know about HIV and HIV testing?” (in English or Spanish) on a tablet computer in the ED while the RA waits. They will listen to the audio components using disposable headphones.Arm (2): HIV/AIDS and HIV testing pictorial brochure: Participants in Arm 2 will be provided with a copy of our HIV/AIDS and HIV testing pictorial brochure (in English or Spanish) to review in the ED. Arm 2 participants will read the brochure while the RA waits. The RAs will not provide clarifications or assistance with the information in the pictorial brochure.

After watching the video or reviewing the pictorial brochure, all patients will complete the post-information questionnaires using the automated telephone key-pad response system (the HIV risk self-perception and value of HIV testing, HIV/AIDS and HIV testing information delivery mode preferences and satisfaction, the HIV/AIDS and HIV testing knowledge, and the HIV risk-taking questionnaires). Patients will receive a re-chargeable gift card for participating.

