#### Primary aims analysis

For Aim 1, we expect that HIV/AIDS and HIV testing knowledge scores can be reasonably approximated by a normal distribution (Table 4). We will compare differences in pre- vs. post- changes in scores between information delivery modes by paired t-tests. If the data are not normally distributed, we will use signed-rank tests. All tests will be executed on an intention-to-treat basis (non-adherence to assigned information delivery mode likely is minimal). Comparisons will first be made for each stratum. MANOVA/ANCOVA will be used for combined samples where language and literacy level are used as stratifying (main) factors. To further account for baseline covariates (e.g., demographic characteristics), a generalized linear mixed-effect model will be fit to the data. The parameters of interest are the coefficients of the dummy variable indicator of study arm assignment and its interactions with language and health literacy level.

**Table 4 Tab4:** Analyses of primary aims

Primary aims	Measurements	Analytic methods
Aim 1. Short-term improvement in HIV/AIDS and HIV testing knowledge **HA1**: 3-way interaction (mode*language*literacy level) **HA2**: 2-way interaction (mode*language or literacy level) **HA3**: no interaction (difference by mode only) **HA4**: no difference	HIV/AIDS and HIV testing knowledge questionnaire at baseline in ED at time of HIV testing, post- vs. pre-information delivery	• Paired t-tests • Signed-rank tests • MANOVA/ANCOVA • Generalized linear mixed-effects regression
Aim 2. Retention of HIV/AIDS and HIV testing knowledge at 3, 6, 9, and 12 months **HA1**: 3-way interaction (mode*language*literacy level) **HA2**: 2-way interaction (mode*language or literacy level) **HA3**: no interaction (difference by mode only) **HA4**: no difference	HIV/AIDS and HIV testing knowledge questionnaire at 3, 6, 9, and 12 months vs. baseline (post-information delivery)	• Paired t-test for each follow-up vs. baseline • Linear mixed-effects regression (assuming constant degradation over time) • Broken-stick linear mixed-effects regression (for non-constant degradation over time)

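### Discontinuing and replacing participants who miss month 3 makes the Aim 2 and 12-month re-testing comparisons conditional on a post-randomisation response

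*Protocol article*

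**What the plan says.** The order of events in the protocol article is as follows.

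- Randomisation comes before the intervention: "We will randomly assign patients in a 1:1 ratio into information delivery mode Arm 1 or Arm 2" (Information delivery and post-information delivery questionnaires).
- The HIV test comes later: "for the study they will have an HIV test after completing the post-information questionnaires" (Rapid HIV testing and assurance of linkage-to-care). Those with a negative result go on: "Potential participants meeting all study eligibility criteria (including a negative HIV test) will be invited to enroll in the longitudinal, randomized, controlled trial" (Follow-up assessments).
- Knowledge is then measured at 3, 6, 9 and 12 months. Under Repeat rapid HIV testing, a re-test is offered at the end of the 12-month assessment.
- The rule at issue, under Follow-up assessments, reads: "Any participants who fail to complete the 3-month post-enrollment follow-up will be discontinued from the study". The next sentence reads: "The recruitment quota will be adjusted to replace them as applicable at their respective study site".

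Table 4 lists the Aim 2 outcome as the knowledge score at months 3, 6, 9 and 12 against the post-information score. Sample size considerations and Table 3 inflate the sample by 25% for attrition. Primary aims analysis plans linear or broken-stick mixed-effects models for Aim 2.

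**The concern.** Completing month 3 happens after randomisation and after exposure to the assigned material, and it is also what makes the first Aim 2 outcome observable. Using it as a condition for staying in the trial means that the arms compared at months 6, 9 and 12 are arms of month-3 responders. If the video and the brochure differ in how many people respond, or in which people respond, those arms are no longer the groups that randomisation formed.

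The rule also turns one missing visit into four missing outcomes: months 6, 9 and 12, and the re-testing offer, which the article calls its main secondary aim. A mixed model can use a participant who misses month 3 and returns at month 6. Here the design ensures that no such participant exists.

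Replacement does not repair this. A replacement is a new person who is kept only on the same condition, so the target fills with responders. The loss that replacement is meant to offset is already provided for in the sample size.

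**Working it through.** **1. The plan's own figure.** Table 3 gives, for Aim 1, 1000 × 1.20 = 1200 and, for Aim 2, 800 × 1.25 × 1.20 = 1200. Both reproduce. The factor 1.25 is the allowance for loss to follow-up, so replacing early losses is a second remedy for part of the same loss. (Read as division by 0.75, the allowance would give 800 / 0.75 × 1.20 = 1280. That is a separate matter and does not affect this point.)

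**2. People outside the count.** Suppose the 1200 is filled with month-3 completers. The article does not say so outright, but it reports progress as 1165 three-month completers. With month-3 loss q, the number followed from the ED is 1200 / (1 − q), rounded up. The article gives no q, so a range is assumed:

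| q | Needed | Outside the 1200 |
|---|---|---|
| 5% | 1264 | 64 |
| 10% | 1334 | 134 |
| 15% | 1412 | 212 |
| 20% | 1500 | 300 |
| 25% | 1600 | 400 |

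**3. Possible shift in the mode contrast.** Let g be the completer mean minus the non-completer mean (same in both arms), and let p_b and p_v be the losses in the brochure and video arms. The completer mean exceeds the all-participant mean by p × g in each arm, so the completers-only contrast shifts by g × (p_b − p_v). All inputs are assumed:

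| g (points) | Loss differs by 2% | 5% | 10% |
|---|---|---|---|
| 1 | 0.02 | 0.05 | 0.10 |
| 2 | 0.04 | 0.10 | 0.20 |
| 3 | 0.06 | 0.15 | 0.30 |

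Against the planned Aim 2 effect of 2.5 points, this is 0.02 / 2.5 = 0.8% to 0.30 / 2.5 = 12%. With p_b = p_v and the same g, the shift is zero.

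**4. Consequence if the modes do not differ (HA4).** Table 3 gives SD 3 and a long-term correlation of 0.4, so the SD of change is 3 × √(2 × (1 − 0.4)) = 3.29. With 75% of 600 per arm, n = 450 and SE = 3.29 × √(2/450) = 0.219. Two-sided type I error is then P(|Z + shift/0.219| > 1.96):

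| Shift | Type I error |
|---|---|
| 0 | 0.05 |
| 0.05 | 0.056 |
| 0.10 | 0.074 |
| 0.15 | 0.105 |
| 0.30 | 0.278 |

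Steps 3 and 4 describe a simple comparison of completers. They overstate what the rule itself adds, because some month-3 non-completers would stay missing without it.

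**The case against.** The strongest reply has four parts.

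*The trigger is not one missed automated call.* Follow-up assessments and Retention of study participants describe reminders by telephone, email and letter, staff-assisted completion, certified letter or courier, visits by two research assistants, and a cellular phone handed over for immediate completion. People still missing after that may be hard to recover. This stands: the number of later visits saved by dropping the rule may be modest. It does not justify ruling those visits out in advance.

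*Intention-to-treat is not broken.* A reader might infer that the rule contradicts "All tests will be executed on an intention-to-treat basis". That sentence sits in the Aim 1 paragraph, the Aim 1 outcome is complete in the ED, and nothing in the article says that ED scores of discontinued participants are deleted. Ending follow-up does not define an analysis set. This stands, and no breach for Aim 1 is claimed here.

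*Test decliners are a different matter.* A reader might also infer that they should be kept in follow-up, since they leave after randomisation. However, a negative test is an inclusion criterion with a stated reason, and patients are told of it in advance: "They also will be informed that their test result must be negative to be enrolled in the longitudinal, follow-up portion of the study". Consent is staged, verbal for the ED questionnaires and signed at testing for follow-up. Willingness to test is part of screening (Table 2), so decliners may be few. Following them would conflict with the criterion and the consent process; reporting them by arm is enough.

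*The sizes are assumed, and reporting is planned.* Both are true. CONSORT reporting of drop-out would disclose the early losses, but it cannot recover outcomes that were never sought.

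**Conclusion.** The point holds for Aim 2 and for re-testing at 12 months. The article states the rule outright, so this is not detail left to an analysis plan. It conditions those comparisons on a post-randomisation response that may differ by arm, and it discards data that the planned models could use.

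The direction and size of any bias cannot be derived from the document. The shifts of 0.02 to 0.30 points rest wholly on assumed loss differences and assumed completer gaps. They are small beside the planned 2.5 points. They matter more if the truth is close to no difference, which the article keeps as one of its four hypotheses. What is certain is the designed loss: every participant discontinued at month 3 contributes nothing at months 6, 9 and 12 and receives no re-test offer.

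**What to change.** 1. Remove the discontinuation rule. Continue contact at 6, 9 and 12 months, and make the 12-month re-test offer, for enrolled participants who miss month 3.
2. Treat any further recruits as additions, not replacements.
3. State that Aim 1 is analysed in all randomised participants with ED scores, by assigned arm.
4. State that the Aim 2 mixed model includes all enrolled participants with any available visit, including month-3 non-completers.
5. Report month-3 non-completers, test decliners and test-positive exclusions by arm.

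The cost is a short amendment, continued tracing and gift-card payments for month-3 non-completers, and a less favourable headline retention rate. With 1165 three-month completers already reported, renewed contact helps only those still within their 12 months. The analysis-set and reporting changes remain possible for everyone.

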#### Repeat rapid HIV testing

As a final step in the 12-month follow-up assessment, all participants will be offered the opportunity to be tested (again) for HIV. Study staff will call these participants and offer to send them a free rapid HIV “home self-test” (OraQuick™ In-home rapid HIV test [55, 56]) to be delivered to the address they select and that they perform themselves. They will be given the alternative of taking the test kit to their study recruitment site and have the RA perform the test for them. We will contact those who elected to undergo HIV testing monthly for up to 3 months to inquire about their use of the test and the test results. Those whose test is preliminary positive will undergo confirmatory testing at their study site.

#### Retention of study participants

RAs will obtain and verify each participant’s contact information (telephone numbers, email addresses, pager/text numbers, mailing and housing addresses, shelters, relatives/friends’ contacts) at enrollment. Within 1 week, we will call each participant, verify their contact information, send a welcome letter and email about the study participation requirements, and remind the participant about the expectations of the study. If a participant cannot be reached, or otherwise fails to perform the follow-up assessments, we will send a certified letter or a courier to their last known address. If needed, two RAs from each study site will go in person to the last known addresses of that participant (home, work, shelter, or relatives/friends’ contacts) to locate them. Two RAs will jointly perform these site visits to ensure their safety. The RAs will either obtain new contact information from the participant or their contacts, or provide the participant with a cellular phone immediately to complete the follow-up assessments.

#### Sample size considerations

The study sample size is *n* = 1200, with equal size strata (*n* = 150) by language, health literacy level, and information delivery mode (Fig. 4). This sample size is based on a 2x2x2 full factorial design and will satisfy the requirements for analysis of the two primary aims and the four alternative hypotheses paired with each aim. The minimum sample size is calculated for a power of 0.80 and a two-sided *α = 0.05* level of significance (Table 3). In general, a larger sample size is needed for greater variation of scores within study arms and strata, lower within-person correlations of scores, and higher loss-to-follow-up. To maximize power, we chose conservative values based upon our prior studies. We increased the sample size by 20% to account for the heterogeneity in patients among the four study sites, and by a conservative additional 25% to account for possible attrition. Based upon other 12-month ED intervention follow-up studies [10], HIV/STD testing studies [57–59], and studies conducted at our own ED [60, 61], a 25% attrition rate at 12 months likely is a worst-case scenario. We expect that our experience and enhanced measures to encourage and facilitate follow-up will result in higher follow-up rates. As of publication of this manuscript, 1165 participants enrolled completed the three-month follow-up.

**Fig. 4 Fig4:**

Sample size by study arm, language, and health literacy level

**Table 3 Tab3:** Sample size rationale by primary aims

Primary Aims	Minimum sample by stratum	Total minimum sample	Rationale and assumptions for minimum sample sizes and final sample sizes for each primary aim
Aim 1. Short-term improvement in HIV/AIDS and HIV testing knowledge ** HA1**: 3-way interaction (mode*language*literacy level) ** HA2**: 2-way interaction (mode*language or literacy level) ** HA3**: no interaction (difference by mode only) ** HA4**: no difference	**125** This **minimum** sample size by stratum will yield a power of 0.80, 0.97 and 0.99 for testing HA1, HA2, HA3 versus HA4 (HA4 as the NULL) Final sample per stratum (information delivery mode, language, and health literacy level) is 150	**1000** The **final sample** after adding 20% to account for the heterogeneity in patients among study sites is **1200** = 1000*(1 + 20%)	• Based on our prior video studies [17, 19, 21], we assume that the scores on the 25-item questionnaire is a normal distribution with a standard deviation of ~ 3 • Before information delivery, mean scores of the two arms are assumed to be the same (due to random assignment) per stratum • Short-term within-person correlation is 0.7 or higher [21] • The pictorial brochure will improve knowledge by an average of 2 points. The video will improve the knowledge by an average of 3.5 points. The effect size is Δ = 3.5–2 = 1.5. (HA3) • 2-way intrxn (mode*language or literacy level) effect size is Δ = 1.5 + 0.75 = 2.25. (HA2), e.g. for those speaking English OR with high health literacy • 3-way intrxn (mode*language*literacy level) effect size is Δ = 1.5 + 0.75 + 0.75 = 3.0, e.g. for those speaking English AND having high literacy AND watching the video
Aim 2. Retention of HIV/AIDS and HIV testing knowledge at 3, 6, 9, and 12 months ** HA1**: 3-way interaction (mode*language*literacy level) ** HA2**: 2-way interaction (mode*language or literacy level) **HA3**: no interaction (difference by mode only) ** HA4**: no difference	**100** This **minimum** sample size by stratum will yield a power of 0.80, 0.97 and 0.99 for testing HA1, HA2, and HA3, versus HA4 (as the NULL)	**800** After adding 25% to account for loss-to-follow-up and 20% for heterogeneity among study sites, the **final sample** size is **1200** = 800*(1 + 25%)*(1 + 20%)	• Long-term within-person correlation is 0.4 or higher • The scores on the knowledge questionnaire in the pictorial brochure arm will degrade to the pre-information baseline level with an average drop of 2 points by 12 months. The score in the video information arm will degrade by an average drop of 1 point. So, compared to baseline, the difference (effect size) in long-term retention of information in the video arm as compared to the pictorial brochure arm is Δ = (3.5–1)-(2–2) = 2.5. • We will assume a similar effect size for 2- and 3-way interactions

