During 2004–2005, we produced a professional quality, animated and live-action, 9.5 min, English-language HIV/AIDS and HIV testing informational video, “Do you know about rapid HIV testing?” [17] During 2005–2006, we conducted a randomized, controlled, non-inferiority trial (K23AI060363) to determine if the video was as efficacious in improving HIV/AIDS and HIV testing knowledge as information delivered orally by an HIV test counselor (a RA) among ED patients before rapid HIV testing [19]. After receiving the information from the video or counselor, participants assigned to the video and the orally-delivered information arms had similar mean scores for correct items (20.1 vs. 20.8) on the 26-item HIV/AIDS and HIV testing knowledge questionnaire from the previous pilot study. Also, the majority (94%) of participants in both study arms believed they were “well” or “very well informed” by the information they received [20]. Yet, English-speaking Latino patients had lower mean scores than non-Latinos, regardless of watching the video or having received information orally. This difference persisted even when controlling for years of education.

In 2010, we began a second study (R21NR011997) to adapt our English-language video, “Do you know about HIV and HIV testing?” into a 15-min Spanish-language video, “¿Qué sabe usted sobre el VIH y sobre las pruebas del VIH?” through a rigorous multi-step process. We conducted two rounds of cognitive-based assessments and pilot testing of the video and accompanying HIV/AIDS and HIV testing knowledge questionnaire among 18–64-year-old Latinos (*n* = 120) at three non-clinical community-based organizations (Chicago, Miami, and San Antonio), and three clinical sites of an ambulatory medical clinic (Providence), an ED (Los Angeles), and a department of health clinic (San Juan). In addition, we conducted similar assessments among 30 bilingual (English- and Spanish-speaking) Latino HIV test providers at the respective community-based organizations. We revised the video based on the results of the cognitive-based assessments and the pilot testing. During this process, we also adapted and tested an accompanying 25-item questionnaire designed to assess HIV/AIDS and HIV testing knowledge applicable to the goals of providing CDC-recommended HIV/AIDS and HIV testing information at the time of HIV testing. We verified the utility of the questionnaire through pilot testing and cognitive-based assessments (Cronbach’s α = 0.80).

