We employed the Spanish-language video and questionnaire in a randomized, controlled, non-inferiority trial at an ambulatory medical clinic, an ED, and a community-based organization in Providence evaluating the efficacy of the video vs. comparable orally-delivered information from an HIV test counselor (a RA) in regards to short-term HIV/AIDS and HIV testing knowledge [21]. We enrolled 18–64-year-old primarily Spanish-speakers (*n* = 150) in the trial. Randomization was stratified by health literacy level (lower vs. higher) as measured by the Short Assessment of Health Literacy-Spanish and English (SAHL-S&E), which has strong psychometric properties in assessing health literacy [22]. After the video or orally-delivered information, HIV/AIDS and HIV testing knowledge applicable to CDC recommendations was assessed through audio-computer self-interviews (ACASI) using our previously developed 25-item questionnaire. Of the 150 participants, 39% met criteria for lower health literacy. For all participants, the mean scores for correct items on the questionnaire for the video (20.4; 95% CI: 19.5~ 21.3) and orally-delivered information (20.6; 95% CI: 19.7~ 21.5) groups (Δ = − 0.15; 95% CI: -1.4~ 1.1) were similar, satisfying the a priori non-inferiority criterion. Of those who watched the video, 93% stated that they were well or very well informed, and of those who received information orally, 96% stated that they were well or very well informed. Mean knowledge scores among lower health literacy participants were similar (18.3 [video] vs. 19.6 [in-person]; *p* < 0.30). In multivariable linear regression analyses, lower mean knowledge scores were related only to health literacy level (β − 2.4; 95% CI: -3.8, − 1.1), and not demographic characteristics (age, gender, race, insurance status, years of formal education, nativity, US acculturation), study arm (video or in-person information), study location (ambulatory medicine clinic, ED, or community-based organization) or prior HIV testing.

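### The planning SD of about 3 for the 25-item knowledge score is below the roughly 3.9 implied by the group's own trial in Spanish speakers, so the stated three-way interaction power of 0.80 is probably too high.

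*Protocol article*

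**What the plan says.** In the protocol article, Table 3 (under Sample size considerations) states for Aim 1: "we assume that the scores on the 25-item questionnaire is a normal distribution with a standard deviation of ~ 3". It attributes this to prior video studies [17, 19, 21]. It adds "Short-term within-person correlation is 0.7 or higher" and effect sizes of 1.5 (HA3), 2.25 (HA2) and 3.0 (HA1). At 125 per stratum, this "sample size by stratum will yield a power of 0.80, 0.97 and 0.99 for testing HA1, HA2, HA3 versus HA4 (HA4 as the NULL"). Aim 2 prints the same three powers at 100 per stratum, with a correlation of 0.4 or higher and a 2.5-point effect, and gives no other SD.

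The text of Sample size considerations notes that more variable scores need a larger sample, and then says: "To maximize power, we chose conservative values based upon our prior studies".

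The Background describes the sources. The oral-information pilot [17] used a 26-item questionnaire, and the English-language video trial [19] scored participants "on the 26-item HIV/AIDS and HIV testing knowledge questionnaire from the previous pilot study". The Spanish-language trial [21] enrolled 150 people in two arms and used the 25-item questionnaire. It reports "the mean scores for correct items on the questionnaire for the video (20.4; 95% CI: 19.5~ 21.3) and orally-delivered information" 20.6 (19.7 to 21.5), with a difference of −0.15 (−1.4 to 1.1).

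**The concern.** The article prints enough of trial [21] for a reader to recover the SD of the score that Table 3 plans with, and the recovered value is clearly above 3. Variance enters the sample size as the square of the SD, so 3.9 against 3 is a factor of 1.69 (3.7 against 3 is 1.52). The 20% added for differences among sites does not cover that and was not meant to.

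The interaction hypotheses decide whether delivery mode should be matched to language and literacy. HA4, the null, is interpreted in the Primary aims section as meaning that either mode serves all patients. If the power for the interaction tests is lower than stated, a non-significant interaction is weaker evidence for a single approach than a reader would think.

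**Working it through.** **Inputs.** From Table 3: SD 3, correlation 0.7 (Aim 1) and 0.4 (Aim 2), 125 and 100 per stratum, and the printed powers. From Sample size considerations: two-sided α = 0.05. From the Background on trial [21]: n = 150, arm CI half-widths of 0.9, difference CI half-width of 1.25, 39% lower literacy, literacy coefficient −2.4. Assumption: 75 per arm, because only the total is given.

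**1. SD implied by trial [21].**
- Arm CIs: SD = (half-width / t) × √n = (0.9 / 1.99) × √75 = 3.9. The arms have equal half-widths. If the limits were rounded, the half-width lies between 0.85 and 0.95, giving SD 3.7 to 4.1.
- Difference CI: SD = 1.25 / (1.976 × √(2/75)) = 3.87.
- Reverse check: SD 3 would give half-widths of about 0.69 (arm) and 0.97 (difference), against the printed 0.9 and 1.25.
- Arm split: with SD 3, a half-width of at least 0.85 needs about 50 or fewer participants. Both arms show 0.9, and two such arms cannot total 150. So an uneven split does not rescue SD 3.
- Within literacy level: √(3.9² − 0.39 × 0.61 × 2.4²) = √(15.21 − 1.37) = 3.72.

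**2. Can the printed powers be reproduced?** Not from the printed effect sizes. With 3.0, 2.25 and 1.5 and a change-score SD of 3 × √(2 × 0.3) = 2.32, power exceeds 0.99 for all three. One reading fits Aim 1: ANCOVA residual SD 3 × √(1 − 0.49) = 2.14, a 1.5-point contrast, and SE for HA1 of 2.14 × √(8/125) = 0.542, divided by √2 for HA2 and by 2 for HA3. It gives 0.790 / 0.975 / >0.99. This was found by fitting. It uses a contrast that is not printed for HA1 or HA2, and its HA2 standard error is not that of a two-way interaction in the full sample. It is therefore not used for the main result.

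**3. Formula-free scaling of HA1.** For any normal-theory test with effect and correlation fixed, z_power + 1.96 is proportional to 1/SD. For 0.80 this sum is 0.842 + 1.96 = 2.80. Spending the whole 20% site allowance on the SD multiplies it by √1.2 = 1.095.

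| SD | At the printed minimum n | With the 20% allowance |
|---|---|---|
| 3.9 | 2.80 × 3/3.9 − 1.96 = 0.195 → 0.58 | 0.66 |
| 3.7 | 2.80 × 3/3.7 − 1.96 = 0.31 → 0.62 | 0.70 |
| English 3, Spanish 3.7: √((9 + 13.69)/2) ≈ 3.4 | 2.80 × 3/3.4 − 1.96 = 0.51 → 0.70 | 0.77 |

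The same scaling applies to the printed 0.80 in Aim 2, if that figure also rests on SD 3.

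**4. HA2 and HA3.** Scaling the printed 0.97 gives 0.84 (SD 3.9) to 0.88 (SD 3.7). Scaling 0.99 gives 0.91 to 0.94. But a two-way interaction averaged over the third factor has half the SE of the three-way contrast. In Aim 1 at SD 3.9 under ANCOVA, the three-way SE is 2.785 × √(8/125) = 0.705, so the two-way SE is 0.352. A 1.5-point contrast then gives 1.5/0.352 − 1.96 = 2.30, which is power 0.989. In Aim 2, a 2.5-point full-sample contrast on change scores gives 0.985 at SD 3.9. Both are above the printed 0.97.

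**5. Correlation that would offset the SD in Aim 1.** For change scores, 1 − ρ = 0.3 × 9/15.21 = 0.178, so ρ = 0.82 (0.80 at SD 3.7). For ANCOVA, 1 − ρ² = 0.51 × 9/15.21 = 0.302, so ρ = 0.84 (0.81 to 0.82 at SD 3.7).

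**The case against.** The strongest objection concerns the power figures, not the SD. If the printed 3.0 and 2.25 are the interaction contrasts themselves, Aim 1 power at SD 3.9 is still at least about 0.975 for HA1 and at least about 0.986 for HA2, so nothing would be lost. That is right as arithmetic, but on that reading the printed 0.80 and 0.97 do not follow from the table at all. Either the SD or the printed power needs correcting.

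A second objection is that 3.9 is a post-information SD in primarily Spanish speakers, pooled over literacy. Half of this trial speaks English, no English SD is printed, and the pilot's English post-video mean of 22.8 out of 25 is near the ceiling, which may narrow the spread. This stands, and it is why the mixed case (0.70, or 0.77 with the allowance) belongs beside the lower figures. Studies [17] and [19] may have shown SDs near 3. The article does not print them, and a 26-item form is not thereby irrelevant.

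Third, the correlation is given only as a lower bound, so a value above 0.8 could absorb the difference in Aim 1. This also stands.

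A reader might infer that HA2 power is overstated in both aims, or that HA1 and HA2 power in Aim 1 is 0.57 and 0.85. The documents do not support either as a finding. Those two values come from the fitted reading in step 2 of the working. Extending that reading to Aim 2 also requires a switch from ANCOVA to change scores, because ANCOVA there gives 0.90 for HA1 at SD 3, not 0.80.

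**Conclusion.** The point holds in limited form. An SD of about 3 is not a conservative value for Spanish speakers on the 25-item score: two separate intervals in the Background put it near 3.9, and near 3.7 within literacy level. Taking the printed HA1 power of 0.80 as given, and holding effect and correlation as stated, the corresponding power is about 0.58 to 0.62 at the minimum sample, or about 0.70 if English speakers have SD 3. Spending the site allowance raises these to about 0.66 to 0.70 and 0.77.

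This rests on roughly equal arms in trial [21], on its post-information SD carrying over to this trial's Spanish speakers, and on a correlation at the stated bound. For HA2 and HA3 no direction can be fixed until the contrast and formula are stated. The finding does not show that the trial as a whole is underpowered, nor that the other inputs called conservative are not.

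**What to change.** - Justify the SD in Table 3 by language, and by literacy level where possible, from the prior data.
- Restate the power for HA1, HA2 and HA3 in both aims at n = 1200 over SD 3.0 to 3.9. State the interaction contrast in points, the formula, and the correlation used, so that the printed powers can be reproduced.
- In Sample size considerations, do not describe the SD as conservative. The statement may stay for inputs that it fits.
- Report the interaction estimates with 95% CIs, and say that a non-significant interaction will not be read as support for HA4.

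The cost is a recalculation and some wording. The article reports that 1165 participants had already completed the three-month follow-up, so no extra enrolment or design change is asked for. The only price is a stated power that is probably less favourable.
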